# An omics-based strategy using coenzyme Q10 in patients with Parkinson’s disease: concept evaluation in a double-blind randomized placebo-controlled parallel group trial

**DOI:** 10.1186/s42466-019-0033-1

**Published:** 2019-08-23

**Keywords:** Parkinson’s disease, Coenzyme Q10, Personalized medicine, *PINK1*, *Parkin*, Mitochondrial dysfunction

## Abstract

**Background:**

This study focuses on genetically stratified subgroups of Parkinson’s disease patients (PD) with an enrichment of risk variants in mitochondrial genes,who might benefit from treatment with the “mitochondrial enhancer” coenzyme Q10 (156 mg coenzyme Q10/d [QuinoMit Q10® Fluid] over six months). The study will be performed in a double-blind, randomized, and placebo-controlled parallel group manner.

**Methods:**

PD patients will be specifically identified and assigned to treatment groups stratified by their genetic “mitochondrial risk burden” and consequently expected mitochondrial dysfunction and treatment response to coenzyme Q10 (homozygous or compound heterozygous *Parkin/PINK1* mutation carriers [P++], heterozygous *Parkin/PINK1* mutation carriers [P+], “omics” positive [omics+], and “omics” negative PD patients [omics-]). The primary endpoint is the change in motor symptoms over six months (as measured by the change in the motor subscore of the MDS-UPDRS). Secondary clinical endpoints include motor fluctuations, non-motor symptoms, results of magnetic resonance imaging of brain energy metabolism (31P-magnetic resonance spectroscopy imaging), and changes in structural and functional brain anatomy (MRI).

**Perspective:**

This study may be a first step towards a successful prediction of treatment response based on the genetic status of PD patients and translate progress in molecular genetics into personalized patient care. Further, magnetic resonance spectroscopy imaging may help quantify increased energy supply objectively and within a brief time after the start of treatment. Therefore, the potential of MRSI also for other studies addressing brain energy metabolism may will be assessed.

**Trial registration:**

This study was registered at the German Clinical Trial Registry (DRKS, DRKS00015880) on November 15th, 2018.

## Background

Despite rapid advances in Parkinson’s disease (PD) research, in particular in the elucidation of etiologic contributions, no disease-modifying therapy has become available to date, and the translation of these advances into improvements in patient care has proven challenging [9]. Although the treatment of motor symptoms is highly effective and can lead to a significant improvement over many years, it remains purely symptomatic and becomes increasingly difficult in the later course of the disease. Since the discovery of the first monogenic forms, it is commonly known that PD is etiologically heterogeneous [1], and there is no doubt that both genetic and environmental factors contribute to the multifactorial genesis. Although the first personalized medicine approaches through gene-specific therapeutic strategies are emerging, there remains a pressing need for disease-modifying approaches. The importance of a disease-modifying therapy is undisputed, and the heterogeneity of the disease on both a clinical and an etiological level has been demonstrated. Previous approaches employing neuroprotective therapies have yielded disappointing and heterogeneous results. Two main hypotheses are posed to explain these findings:
Due to a long prodromal phase, the underlying pathophysiological process is already advanced once first motor symptoms occur, therefore and, thus, any treatment in the symptomatic phase of PD may exert only limited influence on disease progression.Given the heterogeneity of the disease, specific pathophysiology-based treatment approaches for subgroups are required.

The clinical study presented here focuses on the second point and aims to evaluate the efficacy of coenzyme Q10 in a specific subgroup of PD patients. Several clinical trials with coenzyme Q10 in PD patients have already been performed. Published results on the efficacy of coenzyme Q10 given to unselected PD patients are heterogeneous arguing that a global efficacy for all PD patients seems questionable [2, 8]. Coenzyme Q10 has antioxidant properties, which could mediate global efficacy, and additionally acts as a mitochondrial electron transporter, which can mediate improvement in mitochondrial function [10]. Disturbances of mitochondrial function have been proven for hereditary PD caused by mutations in the genes *Parkin* and *PINK1* [5]. The central hypothesis of this study is that coenzyme Q10 is particularly effective for PD patients with expected mitochondrial dysfunction. For this purpose, PD patients will be stratified based on their genetically determined expected mitochondrial dysfunction.

## Methods

### Aim of the trial

The current understanding of the genetic etiology of PD will be used to identify individual patients who would most likely benefit from the aforementioned specific therapy. Coenzyme Q10 as a “mitochondrial enhancer” will be tested in a randomized, double-blind, placebo-controlled parallel group trial. PD patients will be assigned to genetically defined groups stratified by their potential “mitochondrial burden” assuming that individuals with a “higher mitochondrial burden” will likely respond to coenzyme Q10 (homozygous or compound heterozygous *Parkin/PINK1* mutation carriers [P++] > heterozygous *Parkin/PINK1* mutation carriers [P+] > “omics” positive [omics+] and > “omics” negative PD patients [omics-]). The classification of the potential study participants into one of the two omics groups is based on the individual mitochondrial genetic profile. This profile describes PD patients with the highest (omics+) or lowest (omics-) cumulative burden of common genetic variants in genes related to mitochondrial function. This cumulative burden is expressed by a risk score based on eight established single nucleotide polymorphisms (SNPs) for PD (Table 2) [6]. These SNPs have been selected because they are increasing the risk for PD and are functionally linked to mitochondrial homeostasis. This score has been developed within a BMBF-funded collaborative project (MitoPD, 031A430B).

### Study description and study design

The presented study is a multicenter, double-blind, controlled and randomized Phase II study in parallel group design, investigating the treatment of PD with coenzyme Q10 (156 mg/d QuinoMit® Q10 Fluid from MSE Pharmazeutika) in addition to best medical treatment compared to placebo. In each participating study center, potential study participants are examined for their genetic profile before inclusion in the study and assigned to one of the four genetic groups depending on their profile (see Fig. 1). Within the genetic groups, randomization to the experimental group or placebo control group is performed at a ratio of 1:1. The study duration per patient will be six months plus a three-month follow-up period (see Fig. 2). The primary endpoint is evaluated according to the Intention-to-treat (ITT) principle. This is practically implemented with the Full Analysis (FA) dataset (ICH E9, 1998), i.e., all registered patients who are included in the study and randomized are included in the analysis in the treatment group to which they were randomized. For the evaluation of safety, all registered and randomized patients who have received the investigational product (QuinoMit® Fluid or placebo) at least once are considered. The Per Protocol (PP) population is investigated in secondary analyses (sensitivity analyses). In the placebo group, this population consists of patients who have taken at least 80% of the investigational product. In the study group, the PP population consists of patients who took at least 80% of the investigational product and additionally had a coenzyme Q10 plasma level of at least 2.5 μg/ml at follow-up times three months and six months after randomization. The primary hypothesis of the study is that the motor symptoms of patients receiving coenzyme Q10 (QuinoMit Q10® Fluid) differ from those receiving placebo in the form of a linear difference in effect between omics-, omics+, P+, and P++.

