### Outcome measures

The primary endpoint of the study is the change severity of PD motor symptoms after six months of treatment. The primary endpoint is measured as the difference between Part III of the revised version of the Unified Parkinson’s Disease Rating Scale (MDS-UPDRS) six months after randomization and baseline measurement. The minimally clinically relevant difference of the UPDRS III score in PD patients has been investigated in many studies providing heterogeneous results. The type I-error is set to 5% (two-sided). No previous study has taken the genetic status of PD patients into account when investigating the efficacy of coenzyme Q10. The parameters used for the power analysis are based on the work of Shulman et al. [7]. If the clinically relevant difference in the UPDRS Part III in the P++ group is large (mean = 38, standard deviation (SD) = 13.4) and there is no difference in the omics- group (mean = 27.2, SD = 13.4), while the P+ group and the omics+ group have intermediate values (mean = 34.4 and 30.8 with both SD = 13.4, respectively, the power to detect a negative slope of the interaction in the linear regression is 56% if 12, 12, 24, and 24 patients are randomized 1:1 within the four genetic groups P++, P+, omics+, and omics-. If the effect size is 1, which corresponds to a linear trend and a mean UPDRS III of 40.6 in the P++ group, the power of the study increases to 76%. We do not expect any study-related loss of patients (lost to follow-up) for the monogenetic groups (P++ and P+), as these patients have been in regular contact with the trial centers for several years. For the two omics groups, we expect patients lost to follow-up of 5%. This was the median in the four randomized clinical trials of coenzyme Q10 in PD patients conducted to date [4]. The work of Goetz et al. [3] compares the MDS-UPDRS with the original UPDRS and reports a high correlation between scales, especially for the motor part III (r = 0.96, R2 = 0.92). The case number determined for the UPDRS Part III is therefore adjusted by the factor 1/R2, resulting in a case number of approximately eighty-four patients, with approximately fourteen patients each in the two monogenic groups and approximately twenty-eight patients each in the two omics groups. Secondary clinical endpoints include quality of life (Parkinson’s Disease Quality of Life Questionnaire [PDQ39]), depression (Beck’s Depression Inventory II, BDI II), motor fluctuations and disease-related complications (MDS-UPDRS IV), daily activities (MDS-UPDRS II), fatigue (Fatigue Severity Scale [FSS]), sleepiness (Epworth’s Sleepiness Scale [ESS] and Parkinson’s Disease Sleep Scale 2 [PDSS2]), and cognitive function (Montreal Cognitive Assessment [MoCA]) (see Table 1). Secondary endpoints also include magnetic resonance imaging of brain energy metabolism (31P-magnetic resonance spectroscopy imaging [MRSI], see Fig. 3), as well as changes in structural, and functional brain anatomy (MRI). The secondary efficacy endpoints are evaluated in an explorative manner analogous to the primary endpoint. All relevant safety endpoints are described descriptively with suitable statistical measures.

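### The per-protocol set applies a plasma-level filter in the CoQ10 arm only, so the sensitivity analysis compares a more selected active arm with a less selected placebo arm

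*Protocol article*

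**What the plan says.** All the rules below are in the protocol article, section Study description and study design, unless another section is named.

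- Allocation: "Within the genetic groups, randomization to the experimental group or placebo control group is performed at a ratio of 1:1".
- Primary analysis: "The primary endpoint is evaluated according to the Intention-to-treat (ITT) principle", carried out on the full analysis set. The per-protocol set is reserved for secondary analyses, which the article labels sensitivity analyses.
- Per-protocol rule, placebo: "In the placebo group, this population consists of patients who have taken at least 80% of the investigational product".
- Per-protocol rule, CoQ10: "the PP population consists of patients who took at least 80% of the investigational product and additionally had a coenzyme Q10 plasma level". The level must reach 2.5 μg/ml or more, and the timing is given as "at follow-up times three months and six months after randomization".

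The primary hypothesis in the same section is a linear trend in the treatment effect across the four genetic groups, from omics- to P++. Under Genetic stratification, the article also plans exploratory analyses of the secondary endpoints within each genetic group.

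**The concern.** Plasma level at months 3 and 6 is a post-randomisation measurement. It can depend on absorption, on true as opposed to reported intake, and on whether the sample was taken. Any of these may be related to how the patient's motor score would have moved anyway. The filter removes such patients from the CoQ10 arm, but patients with the same traits remain in the placebo arm because nothing there screens them out. The two per-protocol arms are then no longer comparable by randomisation, even if CoQ10 does nothing.

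At stake is how the sensitivity analysis can be read. It is meant to show whether the intention-to-treat result is robust. Under these rules, agreement between the two could be false reassurance. A difference seen only in the per-protocol set could be taken for efficacy in adequately exposed patients when it came from selection.

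**Working it through.** **Step 1. The two rules side by side.**

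| Condition | Placebo | CoQ10 |
|---|---|---|
| At least 80% of product taken | required | required |
| Plasma CoQ10 of at least 2.5 μg/ml at month 3 | not required | required |
| Plasma CoQ10 of at least 2.5 μg/ml at month 6 | not required | required |

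The intake condition is the same in both arms. The plasma conditions are not, and they have no placebo counterpart. Read literally, a CoQ10 patient without one of the two samples does not meet the rule.

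**Step 2. Who is treated differently.** Take three patients who meet the recorded 80% intake: one who absorbs poorly, one who over-reports intake, and one who misses the month-3 sample. On CoQ10 each is, or may be, excluded. On placebo each is kept.

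**Step 3. Illustrative size with no drug effect.** The plan gives no figure to reproduce here. Inputs:

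- SD 13.4, from Outcome measures.
- About 84 patients (same section), hence about 84/2 = 42 per arm.
- Share q of the CoQ10 arm excluded by the plasma rule: not given, assumed 10 to 40%.
- Correlation ρ between plasma level and motor outcome in the absence of any drug effect: not given, assumed 0.1 to 0.4.

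If the lowest share q on a normally distributed variable is removed from one arm only, the mean of that arm shifts in absolute size by

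bias = ρ × SD × φ(z_q)/(1 − q),

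where φ is the standard normal density and z_q its q-quantile. The factor φ(z_q)/(1 − q) is 0.195, 0.350, 0.497 and 0.644 for q = 0.1, 0.2, 0.3 and 0.4. In points:

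| q | ρ = 0.1 | ρ = 0.2 | ρ = 0.3 | ρ = 0.4 |
|---|---|---|---|---|
| 0.1 | 0.26 | 0.52 | 0.78 | 1.05 |
| 0.2 | 0.47 | 0.94 | 1.41 | 1.88 |
| 0.3 | 0.67 | 1.33 | 2.00 | 2.66 |
| 0.4 | 0.86 | 1.73 | 2.59 | 3.45 |

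Example: 0.3 × 13.4 × 0.497 = 2.00.

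**Step 4. Dependence on the SD.** The article gives 13.4 alongside score-level means (27.2 to 38), whereas the endpoint is a change from baseline. With equal variances and correlation r between baseline and month 6, the SD of change is 13.4 × √(2(1 − r)). This gives 13.4 at r = 0.5, 10.4 at r = 0.7 and 6.0 at r = 0.9 (r assumed). The 2.00 points then become about 1.5 and 0.9 at the two higher correlations.

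**Step 5. Error rate of an overall arm comparison.** For a two-sided 5% z-test of 42 placebo against 42(1 − q) CoQ10 patients, bias/SE = ρ × φ(z_q)/(1 − q) ÷ √(1/42 + 1/(42(1 − q))). The SD cancels. Over ρ = 0.1 to 0.4 the rejection rate under no effect is 5.1 to 6.4% at q = 0.1, 5.3 to 9.3% at q = 0.2, 5.5 to 13.1% at q = 0.3 and 5.8 to 17.6% at q = 0.4. This takes all placebo patients as meeting the intake rule. It describes an overall comparison, not the trend test.

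**Step 6. The trend across groups.** If the bias is the same amount b in all four genetic groups, each group's treatment difference shifts by b and the slope across groups shifts by 0. The slope moves only if q or ρ differs between groups.

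**Step 7. Numbers left.** With 60 to 90% retained, 42 × 0.6 = 25 to 42 × 0.9 = 38 CoQ10 patients remain. In each monogenic group (about 14 patients, so about 7 per arm) 4 to 6 remain, before any intake exclusions.

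**The case against.** The strongest reply is that little hangs on this. The primary analysis is by intention to treat, the per-protocol set is secondary, and a disagreeing per-protocol result would not overturn the trial's conclusion. That stands and limits the weight of the point. It does not defend the rule, because a sensitivity analysis that can create a difference by selection cannot show robustness.

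Four stronger readings are tempting, and the documents do not support them.

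- A reader might infer that the placebo arm is unselected. It is not: the 80% intake rule applies there too. It is less selected.
- A reader might infer that everyone who leaves the study drops out of the active arm only. Most early leavers in either arm would fail the intake rule. Table 1 places blood analyses and MDS-UPDRS III at the same month-6 visit, so a patient who misses it lacks the observed primary outcome in either arm. The asymmetry is clearest for low absorbers, over-reporters and single missed samples.
- A reader might infer that the trend estimate is biased. That needs attainment of the threshold, or its link to prognosis, to differ by genetic group. The article gives no attainment rates and no reason to expect such a difference.
- A reader might set the illustrative bias against the 3.6-point step between groups in the power calculation (for example 30.8 − 27.2). That step is a slope quantity, to which a common bias contributes nothing, so it is the wrong yardstick.

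It is also fair to say that ρ and q are assumed, and that the direction of bias is as unknown as its size. A CoQ10 threshold cannot be mirrored in the placebo arm, so the sponsor could not have made the plasma rule symmetric. This is a reason to take it out of the set definition.

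**Conclusion.** The point holds for the secondary per-protocol analysis only. The article states outright an additional post-randomisation entry condition for one arm. As a result, overall and group-specific treatment differences in that set can arise without any drug effect. Under the assumptions shown (ρ 0.1 to 0.4, 10 to 40% excluded, SD 13.4) the spurious overall difference is about 0.3 to 3.5 points, and it scales down with the SD of change. These are illustrations; the documents fix neither size nor direction. The intention-to-treat primary analysis, the sample size and the power are untouched. The slope is affected only under the condition given in Step 6. The change is worth making because it is cheap, and it does not bear on the validity of the primary result.

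**What to change.** Define the per-protocol set by the same rule in both arms: at least 80% of the product taken, with identical handling of missing visits. Remove the plasma criterion from the definition. Report plasma level in a separately labelled exploratory exposure analysis. If a complier-average estimate is used there, with the randomised arm as instrument and 2.5 μg/ml as the exposure cut-off, it must state its assumption that CoQ10 has no effect below that level. Group-level estimates would rest on about 7 patients per arm in each monogenic group and should be presented as unstable. Make the change before unblinding so that it cannot look data-driven.

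The cost is a revised population definition and one extra exploratory analysis. No additional patients or samples are needed, since the current definition already relies on the month-3 and month-6 levels. The sponsor gives up a per-protocol set made up only of patients with proven exposure. An intake-based set is still a post-randomisation selection and so is not free of bias, but both arms then pass through the same filter.

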**Fig. 1 Fig1:**
[figure not shown]
Treatment groups and their respective size

**Fig. 2 Fig2:**
[figure not shown]
Overview on the time schedule of this clinical trial. The intermittent phone calls are not shown for better readability

### Arms and interventions

It is being investigated whether an improvement in motor function and mitochondrial bioenergetics can be achieved by administering 156 mg coenzyme Q10/d (QuinoMit Q10® Fluid) over six months compared to placebo. Coenzyme Q10 is approved as a dietary supplement but at a lower dosage. The substance has already been tested in clinical trials in PD patients but with less specified hypotheses.

### Outcome measures

The primary endpoint of the study is the change severity of PD motor symptoms after six months of treatment. The primary endpoint is measured as the difference between Part III of the revised version of the Unified Parkinson’s Disease Rating Scale (MDS-UPDRS) six months after randomization and baseline measurement. The minimally clinically relevant difference of the UPDRS III score in PD patients has been investigated in many studies providing heterogeneous results. The type I-error is set to 5% (two-sided). No previous study has taken the genetic status of PD patients into account when investigating the efficacy of coenzyme Q10. The parameters used for the power analysis are based on the work of Shulman et al. [7]. If the clinically relevant difference in the UPDRS Part III in the P++ group is large (mean = 38, standard deviation (SD) = 13.4) and there is no difference in the omics- group (mean = 27.2, SD = 13.4), while the P+ group and the omics+ group have intermediate values (mean = 34.4 and 30.8 with both SD = 13.4, respectively, the power to detect a negative slope of the interaction in the linear regression is 56% if 12, 12, 24, and 24 patients are randomized 1:1 within the four genetic groups P++, P+, omics+, and omics-. If the effect size is 1, which corresponds to a linear trend and a mean UPDRS III of 40.6 in the P++ group, the power of the study increases to 76%. We do not expect any study-related loss of patients (lost to follow-up) for the monogenetic groups (P++ and P+), as these patients have been in regular contact with the trial centers for several years. For the two omics groups, we expect patients lost to follow-up of 5%. This was the median in the four randomized clinical trials of coenzyme Q10 in PD patients conducted to date [4]. The work of Goetz et al. [3] compares the MDS-UPDRS with the original UPDRS and reports a high correlation between scales, especially for the motor part III (r = 0.96, R2 = 0.92). The case number determined for the UPDRS Part III is therefore adjusted by the factor 1/R2, resulting in a case number of approximately eighty-four patients, with approximately fourteen patients each in the two monogenic groups and approximately twenty-eight patients each in the two omics groups. Secondary clinical endpoints include quality of life (Parkinson’s Disease Quality of Life Questionnaire [PDQ39]), depression (Beck’s Depression Inventory II, BDI II), motor fluctuations and disease-related complications (MDS-UPDRS IV), daily activities (MDS-UPDRS II), fatigue (Fatigue Severity Scale [FSS]), sleepiness (Epworth’s Sleepiness Scale [ESS] and Parkinson’s Disease Sleep Scale 2 [PDSS2]), and cognitive function (Montreal Cognitive Assessment [MoCA]) (see Table 1). Secondary endpoints also include magnetic resonance imaging of brain energy metabolism (31P-magnetic resonance spectroscopy imaging [MRSI], see Fig. 3), as well as changes in structural, and functional brain anatomy (MRI). The secondary efficacy endpoints are evaluated in an explorative manner analogous to the primary endpoint. All relevant safety endpoints are described descriptively with suitable statistical measures.

**Table 1 Tab1:** Overview on clinical assessments for each study visit

time (months)	visit	clinical assessments
−3-0	screening	MDS-UPDRS III Timed up and go test 10-m-walk test vital signs (safety) blood analyses MDS-UPDRS I, II, and IV PDQ39, BDI II, FSS, ESS, PDSS2, MoCA informed consent check of inclusion/exclusion criteria
0	start visit	MDS-UPDRS III Timed up and go test 10-m-walk test vital signs (safety) blood analyses MDS-UPDRS I, II, and IV PDQ39, BDI II, FSS, ESS, PDSS2, MoCA MRI/MRSI
1	phone call 1	interview on AEs/SAEs, inquiry on self-ratings (diary cards)
2	phone call 2	interview on AEs/SAEs, inquiry on self-ratings (diary cards)
3	visit 1	MDS-UPDRS III Timed up and go test 10-m-walk test vital signs (safety) blood analyses MDS-UPDRS I, II, and IV PDQ39, BDI II, FSS, ESS, PDSS2, MoCA
4	phone call 3	interview on AEs/SAEs, inquiry on self-ratings (diary cards)
5	phone call 4	interview on AEs/SAEs, inquiry on self-ratings (diary cards)
6	visit 2 (end of study treatment)	MDS-UPDRS III Timed up and go test 10-m-walk test vital signs (safety) blood analyses MDS-UPDRS I, II, and IV PDQ39, BDI II, FSS, ESS, PDSS2, MoCA MRI/MRSI
9	follow-up visit	MDS-UPDRS III Timed up and go test 10-m-walk test vital signs (safety) blood analyses MDS-UPDRS I, II, and IV PDQ39, BDI II, FSS, ESS, PDSS2, MoCA MRI/MRSI

*AE* adverse event, *BDI II* Becks Depression Inventory II, *ESS* Epworth’s Sleepiness Scale, *FSS* Fatigue Severity Scale, *MDS-UPDRS* Movement Disorders Society Unified Parkinson’s Disease Rating Scale, *MoCA* Montreal Cognitive Assessment, *MRI* Magnetic Resonance Imaging, *MRSI* Magnetic Resonance Spectroscopy Imaging, *PDQ39* Parkinson’s Disease Quality of Life Questionnaire (39 items), *PDSS2* Parkinson’s Disease Sleep Scale 2, *SAE* serious adverse events

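### The primary model as described names no baseline term; specifying adjustment for the start-visit MDS-UPDRS III would gain precision at almost no cost

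*Protocol article*

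**What the plan says.** Outcome measures defines the primary endpoint as a change score in MDS-UPDRS Part III, taken between "six months after randomization and baseline measurement". The regression is mentioned only in the power text of that section: "the power to detect a negative slope of the interaction in the linear regression is 56"%, with "12, 12, 24, and 24 patients are randomized 1:1 within the four genetic groups" P++, P+, omics+ and omics-. For a larger effect the power is put at 76%. The error rate is fixed by "The type I-error is set to 5% (two-sided"). Study description and study design gives the matching hypothesis, a linear difference in treatment effect from omics- to P++, and the allocation: "Within the genetic groups, randomization to the experimental group or placebo control group is performed at a ratio of 1:1".

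No section lists the terms of the primary model. Nothing says that the baseline score is included, and nothing says that it is excluded. Table 1 has MDS-UPDRS III measured at screening, at the start visit and at months 3, 6 and 9, so a baseline covariate will be on file for every patient who attends the start visit.

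**The concern.** Taking month 6 minus baseline fixes the coefficient on baseline at 1. When the score is measured with error or fluctuates, the best coefficient is usually below 1, and the unadjusted change score then carries avoidable noise. The test here is an interaction in about 84 patients, for which the article itself quotes only 56% power in its first scenario, so precision is scarce.

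The design is also uneven. P++ has about 14 patients, 7 per arm, and sits at the end of the score where it counts most. Randomising within genetic group balances the arms for group but not for baseline motor severity inside P++. A chance difference in baseline between two arms of 7 feeds partly into an unadjusted change-score contrast.

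**Working it through.** **Inputs from Outcome measures.** Group sizes 12, 12, 24 and 24 (N = 72), 1:1 within group; two-sided 5%; P++ "mean = 38, standard deviation (SD) = 13.4"; "no difference in the omics- group (mean = 27.2, SD = 13.4"); P+ 34.4 and omics+ 30.8. With scores 0 (omics-) to 3 (P++), the slope is (38 − 27.2)/3 = 3.6 per step. In the second scenario it is 13.4/3 = 4.467. The baseline to month-6 correlation r is not in the document; 0.5 to 0.9 is assumed.

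**Step 1. Reproduce the stated power.** Six regressions without baseline were tried, one- and two-sided, by non-central t with SD 13.4.

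- Intercept plus treatment × score product only: the sum of squares of the product is 90 − 42²/72 = 65.5; SE = 13.4/√65.5 = 1.656; non-centrality 3.6/1.656 = 2.17 and 4.467/1.656 = 2.70; two-sided power **57.3% and 75.8%**, close to the stated 56% and 76%.
- Both main effects plus interaction: the sum of squares of the score is 82; SE = 13.4 × √(4/82) = 2.960; two-sided power 22.4% and 31.9%.
- None of the others matches both figures. The nearest, group plus product tested one-sided, gives 55.5% and 71.5%.

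So, with 13.4 used as stated, the only one of these models that returns both figures has no baseline term.

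**Step 2. Gain from baseline adjustment.** With SDs s0 at baseline and s1 at month 6, the change-score variance is s0² + s1² − 2r·s0·s1 and the adjusted variance is s1²(1 − r²). Their difference is (s0 − r·s1)², which is never negative. With s0 = s1 the ratio of adjusted to change-score variance is (1 − r²)/(2(1 − r)) = (1 + r)/2.

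**Step 3. Effect on power.** Slope 3.6 (10.8 points in P++), N = 72, 13.4 read as a single-visit SD. SD of change = 13.4√(2(1 − r)); adjusted SD = 13.4√(1 − r²). Change score: intercept, linear group, treatment and interaction (68 df). Adjusted: baseline added and group as a four-level factor (65 df).

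| r | variance ratio | SD change | SD adjusted | power, change | power, adjusted | gain (points) |
|---|---|---|---|---|---|---|
| 0.5 | 0.75 | 13.40 | 11.60 | 22.4% | 28.3% | 5.9 |
| 0.6 | 0.80 | 11.99 | 10.72 | 26.8% | 32.2% | 5.4 |
| 0.7 | 0.85 | 10.38 | 9.57 | 34.1% | 38.9% | 4.9 |
| 0.8 | 0.90 | 8.47 | 8.04 | 47.5% | 51.5% | 4.0 |
| 0.9 | 0.95 | 5.99 | 5.84 | 76.5% | 78.5% | 2.0 |

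In patients, an unadjusted analysis needs 1/0.75 = 1.33 to 1/0.95 = 1.05 times as many for the same precision.

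**Step 4. Where imbalance bites.** The mean score is 84/72 = 1.167. P++ contributes 12 × (3 − 1.167)² = 40.3 of the 82 units of information on the slope, or 49%; P+ contributes 8.3, or 10%. With 7 per arm, the chance baseline difference between P++ arms has SD 13.4 × √(2/7) = 7.2 points. An unadjusted change score carries (1 − r) of it into the contrast: 3.6 points at r = 0.5, 2.1 at 0.7 and 0.7 at 0.9, against an assumed effect of 10.8.

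**The case against.** The strongest objection is that the omission is read from silence. This is a condensed article, the full protocol and analysis plan are not shown, and a covariate list is often kept there. A change-score endpoint does not imply an unadjusted analysis either: regressing change on baseline gives the same treatment and interaction estimates as regressing the month-6 score on baseline. This stands. A reader might infer that the trial will leave baseline out, or that genetic group enters only as a linear score. The document says neither; its linear wording concerns the treatment effect, not the coding of the group main effect.

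Nor does Step 1 settle what the analysis will be. It shows how the trial appears to have been sized. The match also depends on using 13.4 unreduced: a main-effects model with baseline and r = 0.83 (residual SD 13.4 × √(1 − 0.83²) = 7.47) would give 57.5% and 76.0%. But no correlation is reported anywhere, so nothing in the text points to that route.

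A reader might also infer that regression to the mean biases the result. It does not. The listed eligibility criteria set no MDS-UPDRS III threshold, and average drift is shared by arms randomised within group. What remains is chance imbalance, which widens the standard error.

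Finally, the size is uncertain and modest. The (1 + r)/2 formula needs equal SDs; the gain vanishes if r·s1 = s0. At high r only about 2 points are at stake, and the absence of main effects from the model that reproduces the power is a separate and larger matter.

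What survives is that the text as published describes a less precise test than the collected data allow, and that a definite better model is available.

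**Conclusion.** The point holds as a free improvement, not as an error in the document. The primary model as described names a change score and an interaction slope but no baseline term. Adding the start-visit score would bring the residual variance to 0.75 to 0.95 of its unadjusted value and add about 2 to 6 power points at the 10.8-point effect. These figures assume r between 0.5 and 0.9, equal SDs at the two visits, 13.4 as a single-visit SD, and main effects in the model. Protection against chance baseline imbalance is most useful in P++, which carries about half the information on the slope.

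The absolute power levels in the table should not be read as the trial's true power, because they move with the assumed r far more than with the adjustment. The conclusion rests on the difference between the two columns. If the unseen analysis plan already adjusts for baseline, only confirmation is needed.

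**What to change.** State the primary model explicitly: change in MDS-UPDRS III (or the month-6 score) regressed on the start-visit MDS-UPDRS III, genetic group as a four-level factor, treatment, and treatment × ordered group score (0 to 3), with the two-sided 5% test on the last term. Name the start visit as the baseline, since screening also yields a score. The change endpoint can stay as it is.

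The cost is one sentence and three degrees of freedom compared with a model holding linear group, treatment and their interaction (65 instead of 68 at N = 72). No new visit or measurement is needed. The quoted 56% and 76% should then be recalculated for this model with the assumed correlation stated.
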